## Methods/design

### Design

The protocol is for a randomized, single-center feasibility trial comparing the prenatal MBSR program as an add-on to usual care with usual care alone. Participants will be randomized in a 1:1 ratio to an intervention or waitlist control group. A completed SPIRIT checklist is available in Additional Files and the study flow is outlined in Fig. 1. Self-report measures will be collected at three time points: (1) at baseline prior to randomization, (2) immediately after completion of the prenatal MBSR program, and (3) 3 months post-completion. Participants in the waitlist control group will be offered participation in a MBSR program after completion of the study.

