### Secondary feasibility outcome

The secondary feasibility outcome includes the possible effects of the prenatal MBSR program as estimated by self-report measures assessing stress, anxiety, depression, well-being, decentering, reflective functioning, mindfulness, and compassion. The questionnaire packet is built and managed via REDCap (Research Electronic Data Capture) hosted by Aarhus University. Reminders will be emailed after 1 week in case of non-response.

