### Sample size

The study will include a total of 60 participants. This sample size is justified based on the design and objectives of the study [38].

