### Randomization

Eligible participants will be randomized in a 1:1 ratio to either prenatal MBSR + usual care or usual care alone using the REDCap randomization module hosted by Aarhus University. REDCap is a secure, web-based application designed to support data capture for research studies [39]. A data manager from Aarhus University, not otherwise involved in the study, programs the randomization algorithm. Inclusion and thus randomization will take place consecutively until the estimated number of participants is reached.

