### Data analyses

Statistical analyses will be performed using SPSS for Windows (version 27; IBM Corp, Armonk, NY). Skewness, kurtosis, and visual inspection of normal Q-Q plots will be used to inspect normality. Descriptive statistics will be presented as mean and SDs or median and interquartile range (IQR) depending on the distribution of the continuous variables or as frequencies for categorical variables.

Recruitment, participation, and retention rates will be reported and presented in a CONSORT flow diagram [40]. Data collected on numbers of eligible participants recruited, numbers randomized, adherence to, and compliance with the intervention, as well as dropouts lost to follow-up, will be presented as percentages and used to inform the development of a full-scale RCT.

Acceptability of the intervention will be assessed by dropout rates, by computing the mean number of completed sessions, and time spent on at-home practices in the prenatal MBSR group. Participation in ≥ 5 sessions will be considered compliant with the program. A loss to 12-week follow-up analysis will be conducted for age, education, employment, history of a mental disorder, participation in < 5 sessions of the intervention, and pre-scores on the PSS-10 by means of t-test and chi-squared test (χ^2^). A loss to intervention analysis will be conducted for participants attending < 5 sessions of the intervention applying a similar approach.

Analyses of a possible effect of the intervention will be performed based on the intention-to-treat principle, meaning that all participants will be included in the analysis irrespective of their compliance with the intervention protocol. Lastly, an additional per-protocol analysis will be conducted. Since the study is not powered by formal hypothesis testing, only effect estimates and 95% CIs will be presented in accordance with the CONSORT criteria for reporting of feasibility or pilot studies [40].

Independent t-tests (or the non-parametric equivalent Mann-Whitney U) will be conducted to compare the pre- and post-questionnaire scores of the intervention and control groups. In case of skewed distributions in baseline variables, e.g., age and history of mental disorders, logistic regression analyses will be performed.

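### The effect analysis of the self-report scales does not adjust for the baseline score, so its confidence intervals are wider than the planned data allow

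*Protocol article*

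**What the plan says.** The Design section of the protocol article fixes the measurement schedule: "Self-report measures will be collected at three time points: (1) at baseline prior to randomization", then again directly after the program and 3 months later. Each scale therefore has a pre-randomization value by design.

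The Data analyses section states the comparison between arms: "Independent t-tests (or the non-parametric equivalent Mann-Whitney U) will be conducted to compare the pre- and post-questionnaire scores of the intervention and control groups". The results are to be reported as estimates, not tests: "Since the study is not powered by formal hypothesis testing, only effect estimates and 95% CIs will be presented".

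Only one sentence in that section deals with baseline variables in the effect analysis: "In case of skewed distributions in baseline variables, e.g., age and history of mental disorders, logistic regression analyses will be performed". It depends on how the data turn out and does not name the baseline score of the scale being analysed. Logistic regression also needs a categorical outcome, whereas the scales are scored as continuous totals. It therefore does not adjust these effect estimates for baseline.

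The scales are secondary outcomes: "The secondary feasibility outcome includes the possible effects of the prenatal MBSR program as estimated by self-report measures". The trial is small ("The study will include a total of 60 participants") and equally allocated ("Eligible participants will be randomized in a 1:1 ratio to either prenatal MBSR + usual care or usual care alone").

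**The concern.** When an outcome is also measured before randomization, its baseline value is usually a strong predictor of its follow-up value. A two-group comparison of follow-up scores makes no use of that predictor. A comparison of change scores uses it, but with a slope fixed at 1 that is generally too steep. Regression adjustment estimates the slope from the data.

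Two things are at stake. The first is the width of the intervals. The protocol presents effect estimates with 95% CIs in place of formal tests, so the intervals carry the whole message about effect. The second is chance imbalance. With about 30 women per arm, noticeable baseline differences are common, and an unadjusted estimate carries part of any such difference. The study's findings are meant to inform the design of a full trial, so avoidable noise in them has some cost.

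The point concerns a method that the article states, not a detail left to an analysis plan.

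**Working it through.** **Plan's own figure.** There is none to reproduce. The Sample size section gives 60 by reference only, with no SD, effect size, power or correlation.

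**Inputs**
- Total of 60 (Sample size) at 1:1 (Randomization): 60 / 2 = 30 per arm, n = 30.
- 95% confidence level (Data analyses).
- Baseline-outcome correlation r: not in the documents. Assumed 0.3, 0.5 and 0.7.
- Also assumed: equal SD at baseline and follow-up and in both arms, and all 60 women analysed. Results are in SD units.

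**Formulas for the 95% CI half-width**
- Post scores: t(0.975, 58) × √(2/n) = 2.002 × √(2/30) = 2.002 × 0.2582 = 0.517, whatever r is.
- Change scores: t(0.975, 58) × √(2/n × 2(1 − r)).
- ANCOVA: t(0.975, 57) × √(2/n × (1 − r²) × (1 + 1/(2n − 4))). The last factor, 1 + 1/56, allows for estimating the slope.

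For example, at r = 0.5:
- Change scores: 2.002 × √(0.0667 × 1.0) = 0.517.
- ANCOVA: 2.002 × √(0.0667 × 0.75 × 1.0179) = 0.452.

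| r | Post scores | Change scores | ANCOVA | Narrower than post | Narrower than change |
|---|---|---|---|---|---|
| 0.3 | 0.517 | 0.612 | 0.498 | 4% | 19% |
| 0.5 | 0.517 | 0.517 | 0.452 | 13% | 13% |
| 0.7 | 0.517 | 0.400 | 0.373 | 28% | 7% |

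ANCOVA is the narrowest in every row.

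**Simulation check.** Standard errors from 20,000 simulated trials at each r (post / change / ANCOVA) were 0.259 / 0.304 / 0.249 at r = 0.3, 0.258 / 0.258 / 0.225 at r = 0.5, and 0.255 / 0.201 / 0.186 at r = 0.7. They agree with the formulas.

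**Equivalent size.** Leaving aside the small cost of estimating the slope, a post-score analysis would need 60 / (1 − r²) women to match ANCOVA with 60. That is 60 / 0.91 = 66, 60 / 0.75 = 80 and 60 / 0.51 = 118.

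**Sensitivity to missing scores.** With 24 analysed per arm (an assumed 20% loss), the post-score half-width is 0.581 and the ANCOVA half-widths are 0.561, 0.509 and 0.420. The relative gains are almost unchanged.

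**Chance imbalance.** The baseline difference between arms has standard error √(2/30) = 0.258 SD. On one scale, a difference beyond 0.25 SD in either direction has probability about 0.33, and one beyond 0.5 SD about 0.05. Given an observed difference of 0.25 SD:
- the post-score estimate shifts by r × 0.25 = 0.075, 0.125 and 0.175 SD;
- the change-score estimate shifts the other way by (1 − r) × 0.25 = 0.175, 0.125 and 0.075 SD;
- ANCOVA removes the shift.

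**The case against.** The strongest reply is that nothing here is wrong, only less efficient. Over repeated randomizations the unadjusted difference is unbiased, and its 95% CI already allows for chance baseline differences. The outcomes are secondary and exploratory, the primary outcome is feasibility, and no passage says that an effect estimate will set the size of the full trial. All of this stands, and it limits the weight of the point.

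The size of the gain is also uncertain. At a correlation of 0.3 it is only 4% over post scores. A low value is plausible at the last time point: a first consultation at about 18 weeks, nine weekly sessions and about 13 further weeks give 18 + 9 + 13 = 40 weeks, so most women would have given birth by then. If the sentence means change scores, the baseline is used, and at a correlation of 0.7 the gain is 7%, not 28%. This too stands, which is why the range and both comparators are shown. Neither reading overtakes ANCOVA at the assumed correlations.

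A reader might infer three further faults that the documents do not support:
- **Missing scores.** A t-test that omits women without a score does not contradict the intention-to-treat statement. That statement includes participants regardless of compliance and makes no promise about missing data.
- **Mann-Whitney U.** It is not incompatible with reporting estimates and intervals, since the Hodges-Lehmann shift accompanies it. An article may leave the choice of estimator to a fuller document.
- **The 3-month scores.** They are not shown to be left out. The word for post-intervention scores may cover both follow-ups, and a condensed article need not spell this out.

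**Conclusion.** The point holds as one about precision. The stated comparison does not adjust for a baseline score that the trial collects anyway, and on either reading of the sentence a baseline-adjusted analysis gives narrower intervals. With 30 per arm the gain is about 4% to 28% over post scores and about 19% to 7% over change scores, as the correlation goes from 0.3 to 0.7. A chance baseline difference of 0.25 SD moves the unadjusted estimate by about 0.08 to 0.18 SD, in opposite directions for the two readings.

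The figures rest on the assumed correlations, on equal SDs and on complete data. The ranking of methods is firm over that range; the size of the gain is not.

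It would go too far to call the planned analysis biased or invalid. The shift is conditional on the imbalance observed in the one trial that is run, and it averages to zero over randomizations. The imbalance also enters only in part, as r or 1 − r times the baseline difference.

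**What to change.** In the Data analyses section, replace the t-test/Mann-Whitney sentence with wording such as: for each scale, the difference between arms at each follow-up, with its 95% CI, is estimated by linear regression (ANCOVA) or a repeated-measures mixed model, with the baseline score of the same scale as covariate; a bootstrap CI is used if the residuals are markedly non-normal.

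Drop the between-arm comparison of pre scores. Under randomization any such difference is due to chance, and the covariate takes it into account. The conditional logistic regression sentence should not be relied on for this purpose.

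The cost is a change of wording before outcomes are analysed. It needs no new data, visits or participants, and these are routine analyses in the software named in the article. If the article cannot be changed, the same text can go into the statistical analysis plan.

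### The between-arm effect analysis does not use the pre-randomization score as a covariate, so the 95% CIs for the secondary outcomes will be wider than they need to be

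*Protocol article*

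**What the plan says.** The protocol article, Data analyses, names one method for comparing questionnaire outcomes between arms. Independent t-tests, or Mann-Whitney U as the non-parametric alternative, "will be conducted to compare the pre- and post-questionnaire scores of the intervention and control groups". The same section says how the results will be shown: "only effect estimates and 95% CIs will be presented".

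Under Design, self-report measures are taken three times: "at baseline prior to randomization", directly after the program, and 3 months after that. A pre-randomization score on each scale is therefore planned for every woman.

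The pre-score has a named use in one other place. The PSS-10 pre-score is one of the variables compared in the loss-to-follow-up analysis, and the loss-to-intervention analysis follows a similar approach. The only regression named is conditional: "In case of skewed distributions in baseline variables, e.g., age and history of mental disorders, logistic regression analyses will be performed". That sentence does not mention the baseline questionnaire score, and a logistic model does not suit a scale score such as the PSS-10 (0 to 40). It does not supply baseline adjustment.

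Under Sample size: "The study will include a total of 60 participants". Allocation is 1:1.

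**The concern.** The secondary aim is delivered as estimates with confidence intervals, so the width of those intervals largely determines how informative the result is. With about 30 women per arm the intervals will be wide in any case. A woman's own earlier score on the same scale is usually among the better predictors of her later score, and it is already being collected. An analysis that leaves it out, or uses it only by subtraction, gives up precision that costs nothing to keep. It also leaves the estimate moving with whatever chance difference exists between the arms at baseline.

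If the sentence means a separate comparison of pre scores, that part answers no useful question: in a randomized trial, any baseline difference between arms is chance.

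**Working it through.** **Inputs from the document.** 60 women (Sample size), 1:1 (Randomization), so 30 per arm; 95% CIs (Data analyses). The sample size is stated without an SD, effect size or target precision, so the plan has no figure of its own to reproduce.

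**Assumptions.** The baseline-to-follow-up correlation *r* is not in the document; 0.3, 0.5 and 0.7 are used. The SD is taken as equal at both times, the relation as linear, and all 60 women as analysed. The figures concern the t-test; the Mann-Whitney alternative was not calculated.

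**Standard error of a difference between arms, in SD units.** √(2/30) = 0.258.

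**95% CI half-widths.**
- Post scores: t(0.975; 58) × 0.258 = 2.002 × 0.258 = 0.517, whatever *r* is.
- Change scores: 0.517 × √(2(1 − r)).
- ANCOVA: t(0.975; 57) × 0.258 × √(1 − r²) × √(1 + 1/56). The last factor allows for chance imbalance in the covariate.

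| r (assumed) | Post scores | Change scores | ANCOVA | ANCOVA vs post | ANCOVA vs change |
|---|---|---|---|---|---|
| 0.3 | 0.517 | 0.612 | 0.498 | 4% narrower | 19% narrower |
| 0.5 | 0.517 | 0.517 | 0.452 | 13% narrower | 13% narrower |
| 0.7 | 0.517 | 0.400 | 0.373 | 28% narrower | 7% narrower |

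For example, at r = 0.5: 0.452/0.517 = 0.874, or 13% narrower.

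**Simulation check** (4,000 trials at each *r*). Mean half-widths were 0.514, 0.514 and 0.515 for post scores; 0.607, 0.513 and 0.398 for change scores; and 0.495, 0.449 and 0.371 for ANCOVA. These agree with the formulas.

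**Dependence on chance baseline imbalance.** If the arms differ at baseline by one standard error (0.258 SD), the expected shift in the estimate is:
- Post scores, r × 0.258: 0.077, 0.129 and 0.181 SD.
- Change scores, (r − 1) × 0.258: −0.181, −0.129 and −0.077 SD.
- ANCOVA: about zero.

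In the simulation, the correlation between the estimate and the baseline difference was 0.33, 0.50 and 0.70 for post scores; −0.58, −0.50 and −0.37 for change scores; and at most 0.03 for ANCOVA.

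**Lower limit.** At r = 0, ANCOVA gives 2.002 × 0.258 × 1.009 = 0.522, about 1% wider than 0.517. The price of adjusting for an uninformative baseline is negligible.

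**The case against.** Five points can be made for the plan as it stands.

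*The sentence is ambiguous.* A reader might infer that the baseline score is ignored altogether. The text does not establish that. Comparing pre and post scores of two groups can mean comparing change scores, in which case baseline is used and there is no separate baseline test. This stands. It alters the size of the gain but not its direction, since ANCOVA is narrower than both readings at every *r* in the table.

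*The gain may be small.* This also stands. The last measure comes about 9 + 13 = 22 weeks after the program starts. A woman who started at 18 weeks' gestation would then be at about 40 weeks, and the others further on, so many will have given birth. A correlation near 0.3 is plausible there, and the gain over post scores would then be about 4%.

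*Nothing is invalid.* A reader might infer that the estimates are biased. They are not: randomization keeps both unadjusted estimators unbiased on average, and their intervals already reflect chance imbalance. Wider intervals and sensitivity to baseline imbalance are one loss of efficiency seen from two sides, and should not be counted as two harms.

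*Consequences for the full trial.* A reader might infer that the later RCT will be sized from an unadjusted SD and come out too large. No section says so. The article says in general terms that the outcomes will inform that design, and in Data analyses the figures tied to it are percentages for recruitment, randomization, adherence, compliance and dropout. A residual SD or correlation could also be calculated later from the collected data.

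*The stakes are modest.* Feasibility is primary, effects are exploratory, and formal testing is disclaimed. This bears on how urgent the change is, not on which analysis is better.

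The possibility of a separate analysis plan does not dispose of the point, because the article itself names the method.

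**Conclusion.** The concern holds as a matter of precision. The named method is valid on average under either reading, but it is less efficient than adjusting for a score the trial already collects. With 30 per arm, the intervals would be about 4% to 28% narrower than for post scores, and about 19% to 7% narrower than for change scores, as *r* goes from 0.3 to 0.7. Those figures rest on assumed correlations, equal SDs and complete follow-up. The document supports no claim of systematic bias, of baseline certainly being disregarded, or of an oversized later trial. Only secondary, exploratory outcomes are affected; the primary feasibility outcomes are not. The change is worth making because it is nearly free and also removes the ambiguity in the sentence.

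**What to change.** In Data analyses, replace the sentence on independent t-tests and Mann-Whitney U with one linear model per scale and follow-up time point: follow-up score on arm plus the baseline score of the same scale. Report the adjusted mean difference with its 95% CI. Show baseline scores descriptively by arm, without a test. The residual SD and the baseline-to-follow-up correlation can be reported as well, as useful input to the design of the RCT.

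The cost is a rewritten sentence or two and one degree of freedom per model. No new data are needed, and SPSS, which the plan already names, fits these models.

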### Blinding

Group affiliation will be concealed for the researcher performing the statistical analyses.

Participants will not be blinded. Keeping participants blind to this type of intervention would not be possible. Part of the study is to understand if this introduces any difficulties (i.e., resentful demoralization) into the study that would need to be addressed before a larger trial.

### Scientific ethical considerations

Participation in a mindfulness-based program has not been associated with major side effects when the program is delivered by a certified teacher. The Danish Center for Mindfulness, Aarhus University, is affiliated with the Center for Mindfulness at Brown University and collaborates on setting international standards for education and teacher training. In the present study, a psychiatrist and a psychologist will be teaching the prenatal MBSR program. Both have extensive clinical experience and are certified mindfulness teachers. Some side effects have been reported in connection with mindfulness training, such as aggravation of symptoms that could be due to the increased focus on internal states and feelings of losing oneself. If any adverse events should occur, the teachers have the relevant expertise to ensure participant safety or referral to relevant treatment elsewhere. Both teachers are available for individual sessions between the program sessions. Any side effects related to the intervention will be systematically registered by the responsible researcher and published with the results of the study. The possible benefits of mindfulness training in pregnancy as described in earlier sections thus outweighs the potential side effects of the intervention. Moreover, there is a need for more evidence-based, non-pharmacological options for addressing prenatal mental healthcare needs in vulnerable groups for the benefit of both mother and fetus. The adaptations made to the original MBSR program require more research in order to establish an evidence base for the prenatal MBSR program, which is initiated with this feasibility study.

## Discussion

The evidence to date suggest that MBSR and mindfulness-based interventions have great potential in improving mental health in both clinical and non-clinical populations. There is a need for evidence-based and non-pharmacological options addressing mental health during pregnancy. Teaching the skills of mindfulness meditation to a vulnerable group of pregnant women could prove as a viable and non-pharmacological approach, to improve mental health. Moreover, it may provide support in the transition to parenthood. It is anticipated that the findings from the study will access and determine the acceptability and feasibility of the prenatal MBSR program and inform the design of a fully powered randomized controlled trial. The results could also be relevant for other hospitals or healthcare settings working with pregnancy both in and outside of Denmark.

### Status of the study

The study was initiated in mid-January 2021.

### Roles and responsibilities

The Danish Center for Mindfulness, Aarhus University, is responsible for the development and evaluation of the prenatal MBSR program. The developmental and evaluation process is carried out in close collaboration with the outpatient clinic at Copenhagen University Hospital, Amager and Hvidovre. The collaboration includes project meetings every other week and regular meetings with staff at the clinic. Project meetings are held with the responsible parties involved in the *Good Start to Family Life* Project including the management at the outpatient clinic, Oestifterne, and the Danish Center for Mindfulness. The involvement of the staff during the development of the prenatal MBSR program is described in the “The intervention” section. The Danish Center for Mindfulness will have full access to the final dataset.

